## Abstract

**Background:**

Graves’ orbitopathy (GO) is a prevalent manifestation of Graves’ disease (GD), characterized by proptosis, eyelid retraction, soft tissue swelling, diplopia, and potential visual acuity impairment. Furthermore, even mild GO can significantly impact mental health and overall quality of life for patients with GD. Despite its severity, available medical treatments for mild GO are limited. Recent basic studies on orbital fibroblasts suggest hydroxychloroquine (HCQ) as a promising therapeutic agent for GO patients. This randomized controlled trial (RCT) was designed to assess the efficacy of HCQ in treating mild GO.

**Methods:**

This multi-center open-label RCT will be conducted in Taiwan with a total of 108 participants randomized into HCQ and control groups at 2:1 allocation ratio. The primary endpoint of this study is a composite outcome of ophthalmic parameters including eyelid aperture, soft tissue involvement, and exophthalmos. Secondary endpoints comprise changes in quality of life (GO-QoL), orbital volumetry via computed tomography (CT), diplopia scores, clinical activity scores (CAS), visual acuity, and thyroid autoantibodies.

**Discussion:**

This RCT will elucidate the clinical benefits of oral HCQ in patients with mild GO, assessing ophthalmic outcomes, quality of life, disease activity, and thyroid autoantibodies. In addition, data obtained from orbital CT measurements will provide valuable insights into subtle changes in orbital fat and extra-ocular muscle volumes, potentially offering an objective tool for monitoring GO progression.

**Trial registration {2a, 2b}:**

ClinicalTrials.gov NCT05126147. Registered on November 2021. https://clinicaltrials.gov/study/NCT05126147. All items from the World Health Organization (WHO) Trial Registration Data Set are addressed within the relevant sections of this protocol.

**Supplementary Information:**

The online version contains supplementary material available at 10.1186/s13063-025-09002-6.

## Introduction

### Background and rationale {6a}

Approximately 20% of patients with Graves’ disease (GD) suffer from Graves’ orbitopathy (GO). The central pathogenic mechanism of GD is the TSH receptor antibody which causes hyperthyroidism and triggers autoimmune inflammation in the eyes, leading to thickening of the extra-ocular muscles, increased fat deposition, and the accumulation of hyaluronic acid and glycosaminoglycans (GAGs) [1]. These manifestations constitute the typical symptoms of GO, such as swollen and inflamed eyes, exophthalmos, eyelid swelling, diplopia, and even impaired vision. In addition to the physical discomfort, the unpleasant appearance of the eyes caused by GO severely affects patients’ self-confidence, resulting in psychological and social barriers [2]. 

Only half of patients with mild GO naturally improve, and about 20% of them may worsen during follow-up [3]. Unfortunately, there are limited treatment options for patients with mild GO, and the only suggested medical treatment for mild GO is selenium [4]. However, the supporting evidence of selenium in treating mild GO was conducted in the selenium-deficient Europe. Whether selenium is effective in selenium-sufficient region including Taiwan remains unknown [5]. In addition, literature revealed potential association between excessive selenium and certain malignancies and type 2 diabetes mellitus [6], which makes selenium supplementation in selenium-sufficient area more controversial.

In contrast to mild GO, the treatment of sight-threatening or moderate-to-severe GO is more established, with glucocorticoid steroid or orbital surgery as the mainstream strategy, which are often not suitable for mild GO patients [7]. Furthermore, emerging therapies including mycophenolate sodium [8] and teprotumumab [9] focused only on moderate-to-severe and active GO. As a result, a significant proportion of patients with mild GO experience decrease in their quality of life, and there is an unmet need that no effective treatment options are available.

Hydroxychloroquine (HCQ) is a less toxic metabolite of chloroquine and has been increasingly used for long-term and chronic treatment of autoimmune diseases owing to its immune-modulatory effects [10]. One cell study published in *Journal of Clinical Endocrinology and Metabolism* investigated the effect of HCQ on the orbital fibroblasts from 10 patients with mostly mild and inactive GO [2]. Results revealed that HCQ significantly inhibited proliferation, mitotic clonal expansion, adipogenesis, and hyaluronic acid on orbital fibroblasts. However, the evidence of clinical use of HCQ for GO is lacking. Thus, we designed an open-label randomized controlled trial to examine the effect of HCQ in patients with mild GO (NCT05126147).

### Objectives {7}

The objective of this study is to compare the use of oral HCQ versus observation on the ophthalmic outcomes in patients with mild GO. In addition to ophthalmic measurements, quality of life, orbital computed tomography (CT), diplopia score, clinical activity score (CAS), visual acuity, and thyroid autoantibodies including anti-thyroid peroxidase antibodies (anti-TPO), anti-thyroglobulin antibody (ATA), and thyrotropin-binding inhibitory immunoglobulins (TBII) will be recorded for comparison.

### Trial design {8}

This is a multi-center open-label interventional randomized controlled trial (RCT) comparing the effects of HCQ versus observation in patients with mild GO in Taiwan. The allocation ratio of randomization will be 2:1 in HCQ and control group, respectively. This trial adopts a superiority framework, hypothesizing that the addition of hydroxychloroquine to standard of care will result in superior ophthalmic outcomes compared to standard of care alone in patients with mild GO.

## Methods: participants, interventions, and outcomes

### Study setting {9}

Patients with mild GO who have already achieved euthyroidism will be screened at Taipei, Bei-Hu, Cancer Center, and Hsin-Chu branches of National Taiwan University Hospital (NCT05126147). Participants will be enrolled and randomly assigned in a 2:1 ratio to treatment or control group. The treatment group will receive HCQ 200 mg twice daily for a duration of 6 months, followed by a 6-month observation period, while the control group will receive standard of care for GO by endocrinologists. Participants will be enrolled by endocrinologists after screening of the inclusion and exclusion criteria. Ophthalmic measurements will be performed by the same ophthalmologist specializing in GO in each hospital to avoid inter-observer differences. In addition, ophthalmologists will be blinded to the participants’ treatment groups. They will be excluded from any role in allocation or treatment decisions and conducted evaluations according to standardized procedures.

### Eligibility criteria {10}

We estimate enrolling 108 patients with mild GO meeting the following inclusion and exclusion criteria.

#### Inclusion criteria

Participants aged 18 to 75 years.The diagnosis of mild GO established by an endocrinologist and an ophthalmologist based on clinical symptoms, signs, and laboratory data, according to the European Group on Graves’ orbitopathy (EUGOGO) criteria.Participants should achieve euthyroidism for at least 2 months. If they have undergone radioactive iodine treatment due to hyperthyroidism, their thyroid function should be normal for at least 6 months.

#### Exclusion criteria

Participants with moderate-to-severe or sight-threatening GOPregnancyDrug or alcohol abuseInability to comply with the trial requirementsInability to provide informed consentAdministration of HCQ or systemic steroids within 3 months prior to enrollmentHistory of adverse effects related to HCQ such as retinopathyPre-existing retinal disease, including macular pathology (e.g., age-related macular degeneration or diabetic macular edema)Renal insufficiency (estimated glomerular filtration rate (eGFR) less than 60 mL/min) Abnormal liver function (aspartate aminotransferase (AST) or alanine aminotransferase (ALT) more than 2 times the upper limit) Anemia (hemoglobin less than 10 g/dL) Granulocyte deficiency (absolute neutrophil count less than 100/µL) Low platelet count (platelet less than 150 K/µL) G6PD (glucose-6-phosphate dehydrogenase) deficiency Porphyria cutanea tarda Allergy to 4-aminoquinoline compounds

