### Intervention description {11a}

Treatment group will receive HCQ 200 mg twice daily for 6 months. The treatment dosage is commonly used clinically as an initial starting dose, with average serum concentration of 0.3 to 1.9 μM in steady state [12]. The effect of HCQ was supported by one previous cell study of orbital fibroblast derived from patients with GO treated with physiological achievable concentration of HCQ [2]. Both the intervention and control groups will receive the standard of care.

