### Protocol amendments {25}

Any modifications to the protocol that may impact study conduct, participant safety, or study outcomes—including changes to eligibility criteria, outcomes, analyses, or study procedures—will be submitted to the Research Ethics Committee (REC) in National Taiwan University Hospital for review and approval prior to implementation. Substantial protocol amendments will also be updated in the ClinicalTrials.gov registration and communicated to investigators and participants as appropriate. All amendments will be reported in future trial publications.

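### The neutrophil exclusion limit is printed as 100/µL, which would leave severe neutropenia eligible; check it against the approved protocol and raise it if it is the operative limit

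*Protocol article*

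**What the plan says.** The protocol article, Exclusion criteria, lists three blood-count limits:

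- Neutrophils: "Granulocyte deficiency (absolute neutrophil count less than 100" per µL.
- Platelets: "Low platelet count (platelet less than 150 K/µL".
- Hemoglobin: "Anemia (hemoglobin less than 10 g/dL".

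The same list excludes an eGFR under 60 mL/min and liver enzymes above twice the upper limit. No other section gives a different neutrophil limit, a reason for 100/µL, or a neutrophil count at which treatment would stop.

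The list is an operative entry rule. Study setting {9} states: "Participants will be enrolled by endocrinologists after screening of the inclusion and exclusion criteria". Intervention description {11a} gives what follows for those allocated to the active arm: "Treatment group will receive HCQ 200 mg twice daily for 6 months".

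**The concern.** The criterion is labelled as granulocyte deficiency, but the number attached to it catches only counts close to zero. A site that applies it as printed would have no basis in this criterion for turning away a candidate with, say, 300/µL, although the same list rejects a platelet count of 149 K/µL.

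What is at stake is a safety threshold at entry, and the public text that readers and later trials may copy. The trial's inference is not at stake.

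**Working it through.** The limit is a fixed threshold and not a calculated figure, so the article contains no derivation to reproduce. The check is a reading, with one assumed benchmark.

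**1. Is the printed figure intact?** Yes. Number and unit are both present, and the neighbouring entries are complete. Nothing suggests that text was lost in extraction.

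**2. Does it fit its own label?** The article does not define deficiency. Assumption, not from the article: conventional cut-offs lie between 500 and 1500/µL. Printed limit divided by assumed cut-off:

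| Assumed cut-off (/µL) | Printed limit ÷ cut-off | Counts that are deficient but not excluded (/µL) |
|---|---|---|
| 500 | 100/500 = 0.20 | 100 to 499 |
| 1000 | 100/1000 = 0.10 | 100 to 999 |
| 1500 | 100/1500 = 0.07 | 100 to 1499 |

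The ratios only restate the assumed cut-offs. What the table adds is that counts of 100 to 499/µL are deficient and yet pass the criterion at every point of the assumed range, so the conclusion does not depend on which cut-off is preferred.

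**3. Does it fit its neighbours?** The liver limit is scaled in the list itself, at twice the upper limit. The platelet (150 K/µL) and hemoglobin (10 g/dL) limits are read here as acting at mild to moderate abnormality. That reading uses general reference ranges, which the article does not give, so it too is an assumption. On it, the neutrophil limit is the only blood-count limit set at an extreme value.

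**4. Does anything else in the article catch these patients?**

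- Collection, laboratory evaluation, and storage of biological specimens {33} includes a blood count with differential, but that section gives no timing and no action level. The schedule in Table 2 is not visible.
- Interim analyses {21b} provides for continuous adverse event monitoring.
- Criteria for discontinuing {11b} allows stopping for intolerance or documented adverse events.

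These act after entry and do not replace an entry limit.

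**5. Does the limit enter the sample size?** No. Sample size {14} uses 12% against 37%, 2:1 allocation, two-sided alpha 0.05 and 80% power. With the pooled-variance formula and no continuity correction:

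- pooled proportion = (0.12 + 2 × 0.37)/3 = 0.287
- n(control) = [1.960 × √(1.5 × 0.287 × 0.713) + 0.842 × √(0.12 × 0.88 + 0.37 × 0.63/2)]² / 0.25² ≈ 35.2, rounded up to 36
- n(HCQ) = 2 × 36 = 72, total 108, with power 81.0% at that size

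The plan's figures reproduce, and the neutrophil limit plays no part in them.

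**The case against.** The strongest reply has three parts.

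**The benchmark comes from outside.** The article defines no cut-off, so any statement that the limit is too low by some factor follows from the range supplied here. This stands. A reader might infer that the limit has been shown to be 5 to 15 times too low, or that 80% to 93% of deficient patients would be admitted. The article supports neither. The first figure is the assumed cut-off divided by 100. The second is (c − 100)/c for an assumed cut-off c, a share of a number line and not of patients.

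**It may be only a misprint.** This also stands as a possibility. The approved protocol and screening form are not shown, so neither a misprint nor a deliberate choice can be asserted. A wrong safety threshold in the public protocol would still deserve correction.

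**The harm pathway is thin.** Adverse event reporting and harms {22} names rash, gastrointestinal upset, headache and visual symptoms as the known HCQ reactions; neutropenia is not among them. Participants have mild disease and have been euthyroid for at least 2 months. A clinician who sees a count of 300/µL might decline to enrol the patient whatever the list says. This lowers the expected impact considerably. It also blocks the inference that severely neutropenic patients have been enrolled or harmed, for which the article offers no evidence. It does not explain why the protocol names this deficiency as an exclusion and then sets a limit that misses most of it.

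**Conclusion.** The point holds as a question about a stated entry-safety limit. As printed, 100/µL would leave patients with severe neutropenia eligible under this criterion, and it is out of step with the platelet and hemoglobin limits beside it. This rests on an assumed conventional cut-off between 500 and 1500/µL and holds at every value in that range.

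Whether the figure is a dropped digit or the approved limit cannot be settled from the article. The number of candidates affected cannot be estimated from it either; that it is probably very small is a judgement from the population, not a calculation. If the figure is a misprint, no participant need have been affected. Sample size, alpha, power and endpoint are unchanged.

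The point should be acted on because it concerns safety and costs little to resolve. It is not a threat to the trial's validity.

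**What to change.** Compare the printed figure with the ethics-approved protocol and with the screening form in use.

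- **Both give a higher value:** correct the published number. Nothing more is needed.
- **Both say 100/µL:** raise the limit by amendment to a value chosen by the clinical leads, for example 1000/µL within the assumed range of 500 to 1500/µL. Protocol amendments {25} already covers this route, "including changes to eligibility criteria, outcomes, analyses, or study procedures". Then check the baseline neutrophil counts of participants already enrolled against the new limit.
- **Only the screening form says 100/µL:** correct the form and make the same baseline check.

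The cost is one corrected number in the first case. In the second it is one ethics amendment with a registry update and a short query on baseline counts. In the third it is a corrected form and the same query. A raised limit may exclude some further candidates; how many is unknown, but it is unlikely to matter for recruitment. The sample size calculation does not need to be repeated.

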### Who will take informed consent? {26a}

The participants will be required to sign formal informed consents after a full explanation of the details regarding this trial by principal investigators and/or study nurses.

### Additional consent provisions for collection and use of participant data and biological specimens {26b}

Permission of use of personal data, medical record, and biological specimens will be obtained in the formal informed consents.

## Interventions

### Explanation for the choice of comparators {6b}

According to previous epidemiological evidence, around half of the patients with mild GO experience remission spontaneously [6]. Watchful waiting is also recommended as one of the treatment options in the guidelines by EUGOGO, American Thyroid Association (ATA), and European Thyroid Association (ETA) [7, 11]. Selenium was reported to be effective in Europe in one previous study [4], but the effect of selenium on GO in selenium-sufficient region including Taiwan remains unknown [5]. Therefore, we chose observation and standardized care for GO as the comparator in the control group. The standard of care consists of supportive treatment as recommended by EUGOGO guidelines [7], including regular monitoring, local symptomatic relief (e.g., lubricating eye drops), optimization of thyroid function, and lifestyle counseling such as smoking cessation. These approaches represent the current clinical management for patients with mild GO who do not meet criteria for corticosteroid therapy.

### Intervention description {11a}

Treatment group will receive HCQ 200 mg twice daily for 6 months. The treatment dosage is commonly used clinically as an initial starting dose, with average serum concentration of 0.3 to 1.9 μM in steady state [12]. The effect of HCQ was supported by one previous cell study of orbital fibroblast derived from patients with GO treated with physiological achievable concentration of HCQ [2]. Both the intervention and control groups will receive the standard of care.

### Criteria for discontinuing or modifying allocated interventions {11b}

Trial discontinuation will occur under the following conditions for enrolled participants:Disease deterioration during study period requiring further medical treatment or surgical interventionsIntolerance, documented adverse events, or allergy to study drug (i.e., HCQ) in treatment group

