### Outcomes {12}

Primary endpoint of this study is the composite ophthalmic outcome of ophthalmic examinations including eyelid aperture, soft tissue involvement, and exophthalmos at the 24th week and 48th week of study, with definitions in line with the previous literature for comparison [4]. 

The primary endpoint is a composite ophthalmic outcome assessed at weeks 24 and 48. Based on predefined criteria (as shown in Table 1), participants will be classified as follows:Improvement: achievement of at least one improvement criterion in any domain, without meeting any deterioration criteria in the othersDeterioration: meeting any deterioration criterion in one or more domainsStable: neither improved nor deteriorated in any domain

**Table 1 Tab1:** Definition of the composite ophthalmic outcome (primary endpoint)

Ophthalmic domain	Measure	Result classifications		
		Improvement	Stable	Deterioration
Eyelid aperture	Slit lamp	Decrease by ≥ 2 mm	Neither improved nor deteriorated	–
Soft tissue involvement	NOSPECS class 2 signs	Reduction of ≥ 1 grade in NOSPECS class 2 signs		1. Increase ≥ 1 NOSPECS class 2. New NOSPECS class
Exophthalmos	Hertel exophthalmometer	Decrease by ≥ 2 mm		–
Other ophthalmic signs				Vision acuity deterioration or other evidence of optic nerve compression

NOSPECS is a clinical classification system for assessing the severity of Graves’'orbitopathy [7], consisting of the following seven classes (class 0–6):

Class 0: No signs or symptoms; Class 1: Only signs, no symptoms (e.g., lid retraction); Class 2: Soft tissue involvement (e.g., periorbital edema, conjunctival injection, chemosis); Class 3: Proptosis; Class 4: Extraocular muscle involvement; Class 5: Corneal involvement; Class 6: Sight loss due to optic nerve compression

In this study, improvement or deterioration in soft tissue involvement is assessed based on changes in class 2 severity. Deterioration is defined as a worsening of at least one grade in any NOSPECS class, or the appearance of a new class not previously present Improvement: achievement of at least one improvement criterion in any domain, without meeting any deterioration criteria in the others Deterioration: meeting any deterioration criterion in one or more domains Stable: neither improved nor deteriorated in any domain

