### Statistical methods {20a, 20b, 20c}

Basic characteristics will be presented using descriptive statistics, including mean (standard deviation) and number of occurrences (percentage). For non-normally distributed data, the median (interquartile range, IQR) will be used. To compare between the treatment group and the observation group, depending on the nature of the data, Student’s *t*-tests will be used for continuous variables, and chi-square tests or Fisher’s exact tests will be used for categorical variables, to examine the differences between the two groups.

To compare the scores of the GO-QoL and the CAS before and after treatment, two-sided *t*-tests and Mann–Whitney tests will be used. Pearson’s correlation analysis will be utilized to test the association and determine the correlation coefficient (*r*) among variables of interest. The severity of thyroid eye disease before and after treatment in both groups will be compared in terms of the proportion of patients who show improvement, stability, or deterioration. One-way repeated measures analysis of variance (ANOVA) will be used to analyze the change of variables before and after treatment. In addition to ANOVA, ANCOVA and regression models will be used to adjust for baseline differences and estimate effect sizes with confidence intervals.

Exploratory subgroup analyses will be performed to assess whether treatment effects differ by age, gender, baseline TBII levels, duration of GO, and smoking status. These analyses are intended to explore potential effect modifiers and will be interpreted cautiously given the limited sample size. A two-tailed *P* value < 0.05 will be considered statistically significant. Statistical analysis will be performed using Stata/SE 14.0 for Windows (StataCorp, College Station, TX, USA).

All randomized participants, including those who discontinue the intervention prematurely, will be included in the primary analysis based on the intention-to-treat (ITT) principle. Sensitivity analyses will be conducted if necessary to evaluate the robustness of results in the presence of missing data. Missing data will be handled using multiple imputation under the assumption of missing at random (MAR).

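### Deterioration needing further treatment is a reason for discontinuation but is not an endpoint event, so imputation or a later examination can score known failures as Stable or Improvement

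*Protocol article*

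**What the plan says.** Four statements in the protocol article bear on this point.

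- **Criteria for discontinuing or modifying allocated interventions {11b}.** The lead-in is "Trial discontinuation will occur under the following conditions for enrolled participants". The first condition is "Disease deterioration during study period requiring further medical treatment or surgical" interventions, and it is not restricted to one arm. The second (intolerance, adverse events or allergy) is restricted to the HCQ group.
- **Outcomes {12}.** "The primary endpoint is a composite ophthalmic outcome assessed at weeks 24 and 48". A participant falls in the worst category by "meeting any deterioration criterion in one or more domains". Table 1 lists only examination findings under that category; being given further treatment is not among them.
- **Statistical methods {20a, 20b, 20c}, population.** "All randomized participants, including those who discontinue the intervention prematurely, will be included in the primary analysis based on the intention-to-treat (ITT) principle".
- **Same section, missing data.** "Missing data will be handled using multiple imputation under the assumption of missing at random (MAR"). No class of missing outcome is exempted, and sensitivity analyses are promised only if they turn out to be needed.

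No section says whether a participant discontinued for deterioration is still examined at weeks 24 and 48, or how that participant is classified.

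**The concern.** The first discontinuation condition is close to the bad outcome that the primary endpoint exists to count. Two routes lead to misclassification, and they are alternatives for any one participant and visit.

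- **The participant leaves follow-up.** The week-24 or week-48 classification is missing and is imputed. Unless the imputation model uses the recorded deterioration, the draw resembles participants who did not deteriorate, so a known failure can become Stable or Improvement. Intention-to-treat keeps the person in the denominator but does not supply the observed failure.
- **The participant stays and is treated.** Table 1 looks only at the eyes at the visit. Someone who worsened, was treated and then looks better than at baseline can be scored as Improvement.

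The primary comparison is at stake. With 72 and 36 participants, a few reclassified people move the estimate, and an outcome that was never collected cannot be recovered later.

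**Working it through.** **Inputs.** Sample size {14}: 12% improvement in control, 37% on HCQ, 2:1 allocation, two-sided 0.05, 80% power, 72 and 36 participants. Background {6a}: about 20% of patients with mild disease may worsen. The documents give no withdrawal share *w*; 5% to 20% is assumed here. The top of that range treats every worsening as needing treatment, so it is an upper end.

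**Step 1: the plan's own figure.** Pooled-variance formula for two proportions, no continuity correction, k = 2:

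- mean rate = (0.12 + 2 × 0.37)/3 = 0.2867
- n(control) = [1.960 × √(1.5 × 0.2867 × 0.7133) + 0.8416 × √(0.12 × 0.88 + 0.37 × 0.63/2)]² / 0.25² = (1.0855 + 0.3967)² / 0.0625 = 35.2, rounded up to 36
- HCQ 72, total 108, power 81.0%

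The stated 108 reproduces. This point does not alter it.

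**Step 2: which reading does the text support?**

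| Pointing to leaving follow-up | Pointing to stopping treatment only |
|---|---|
| The lead-in in {11b} speaks of discontinuing the trial | The heading of {11b} speaks of allocated interventions |
| The first condition covers controls, who have no study drug to stop | Statistical methods refers to people who stop the intervention early |

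Leaving follow-up is the better-supported reading, but not the only one.

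**Step 3: if they leave and are imputed from same-arm completers.** Let *p* be the true improvement rate, with those who leave counted as non-improvers. All improvers are then among the completers, whose rate is p/(1 − w). Imputing the share *w* at that rate makes the whole arm's rate p/(1 − w).

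| w control | w HCQ | Control | HCQ | Difference (true 25) |
|---|---|---|---|---|
| 5% | 5% | 12.6% | 38.9% | 26.3 |
| 10% | 10% | 13.3% | 41.1% | 27.8 |
| 20% | 20% | 15.0% | 46.3% | 31.3 |
| 20% | 5% | 15.0% | 38.9% | 23.9 |
| 5% | 20% | 12.6% | 46.3% | 33.6 |

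In people, at 10% in both arms: 36 × 0.10 = 3.6 control and 72 × 0.10 = 7.2 HCQ participants are known failures. Of these, 3.6 × 0.133 = 0.5 and 7.2 × 0.411 = 3.0 would be counted as improved. If they were the only deteriorators, all of them would be drawn as Stable or Improvement.

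**Step 4: no true effect, 12% in both arms.** Equal withdrawal gives a difference of 0. With 20% in control and 5% in HCQ it is 0.126 − 0.150 = −2.4 points; reversed, +2.4.

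**Step 5: if they stay and are treated.** Assume 10% are treated and half of those score as improved, adding 5 points to an arm. In both arms this gives 17% v 42%: the difference is still 25 points and power is about 76%. In controls only it gives 17% v 37% and power of about 58%. Both are assumptions.

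**The case against.** The strongest reply is that {11b} may mean only that treatment stops. The statistical section includes those who stop the intervention, no section says that examinations cease, and the schedule in Table 2 is not visible here. On that reading there may be little to impute. This stands as an ambiguity, and it is why the conclusion is conditional. It does not dispose of the point, because Table 1 then scores a treated participant on the later examination alone.

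A second reply is that progression needing treatment would ordinarily meet Table 1, which counts worsening in any NOSPECS class, a new class, or visual loss. That is true if the participant is examined while worse. But the endpoint is read at weeks 24 and 48, and nothing carries an interim deterioration forward to those visits. Someone who deteriorates after week 24 would lose only the week-48 outcome.

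A third is that imputation models and sensitivity analyses usually belong in the analysis plan, which is not shown. Their detail is rightly left there. What the article does fix is MAR for all missing outcomes and an endpoint that omits this event.

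A reader might infer more than the documents support:

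- **That MAR is false by design.** Missingness driven by a recorded deterioration can be MAR if the model uses that record. The article specifies no model. It is fair to say only that MAR is not credible for these participants when the record is ignored.
- **That the bias favours HCQ.** Steps 3 and 4 show that it can go either way or vanish.
- **That power drops to 58%.** That needs treated deterioration to be scored as improvement in controls alone.
- **That the HCQ-only condition adds to the same bias.** Stopping for intolerance can arise only where the drug is given, and intention-to-treat already includes these people. How their outcomes are handled is a separate question.

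**Conclusion.** The point holds in conditional form. Followed as written, the article lets a participant known to have deteriorated enough to need treatment be scored as Stable or Improvement: through imputation if follow-up ends, or through a later examination if it continues. Which route applies is unsettled because {11b} and the statistical section do not agree on what is being discontinued.

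From a true difference of 25 points, the illustration runs from 23.9 to 33.6 points across assumed withdrawal of 5% to 20% per arm, and from 26.3 to 31.3 when withdrawal is equal. These figures rest on two assumptions: those who leave are all non-improvers, and imputation draws on same-arm completers without using the recorded deterioration. A model that uses the record would shrink the error but need not remove it. With equal true rates and equal withdrawal there is no bias. The sample size of 108 is unaffected.

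**What to change.** 1. Reconcile {11b} with the statistical section: state whether discontinued participants are still assessed at weeks 24 and 48. The clinical stopping criteria stay as they are.
2. Add to the primary endpoint definition that deterioration needing further medical or surgical treatment for the orbitopathy before the visit is analysed as Deterioration (non-improver), whatever a later examination shows and whether or not the outcome is missing.
3. Limit multiple imputation under MAR to outcomes missing for other reasons.
4. Replace the conditional promise of sensitivity analyses with a prespecified missing-not-at-random, delta-adjusted analysis.

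The cost is a short amendment and matching wording in the analysis plan. The week-24 and week-48 assessments are already planned. The observed improvement rate may be slightly lower. If the planning rates already treat these participants as non-improvers, they remain 12% and 37% and power stays at 81%. The change is best made before any such outcomes are lost.
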